### Blinding

2.4

Owing to the particularity of clinical acupuncture and moxibustion, it is impossible to use a strict standard blind method for evaluation. Thus, a third party that is blind to the grouping condition carried out the effect evaluation. The efficacy evaluator, the operator and the statistician will be carried out by independent researchers. Subjects, efficacy evaluators, and statistical analysts will be all blinded.

## Participants

3

### Inclusion criteria

3.1

In this trial, only patients meeting all of the following criteria will be included:

(1)The diagnosis of UUI is made by a urologist.(2)The age of the patient is 18 to 75 years.(3)Frequent urination, urgency, and urinary incontinence. Although the patient knows the intention of urination, it is difficult to control urination.(4)No drug treatment during the study and no acupuncture treatment within 1 month prior to the study.(5)Not participating in other clinical studies within 2 weeks prior to this study.(6)Course of disease at least 3 months.(7)Patient's vital signs are stable, and is conscious enough to be examined and treated.(8)Signed an informed consent form to volunteer in the study.

### Exclusion criteria

3.2

(1)Patients with a history of botulinum toxin infection of the bladder or pelvic muscles in the past year.(2)Patients with urinary tract infections or vaginal infections during the study period.(3)Patients undergoing implantable pelvic stimulator therapy during the study period.(4)Electrostimulation applied to patients in the pelvic region, back, and leg areas during the study period.(5)The use of drugs that can influence the outcomes before or during the study.(6)Patients participating in other clinical research related to gynecology, urinary system or kidney function.(7)Participants with coagulopathy or taking anticoagulants.(8)Patients with severe heart, liver or kidney damage, patients during pregnancy or lactation, or patients who are generally in poor condition and are unable to cooperate.(9)Participants with a pacemaker, patients severely afraid of needles, and those fainting or with metal allergy.

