### Participants and recruitment

2.2

A total of 100 participants will be recruited between January 2020 and March 2021 through the Second Affiliated Hospital of Guizhou University of Traditional Chinese Medicine website or via public posters. A researcher is responsible for the recruitment and screening of participants, and a urologist is responsible for the diagnosis. A 2-week baseline assessment will be conducted by the researcher, which will be responsible for assessing and recording the participants’ baseline status. After signing a written informed consent, eligible participants will be assigned with random numbers generated by a third party.

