## Statistical methods and analysis

6

The data are analyzed using the SPSS software, Version 22. 0 (IBM SPSS Statistics, IBM Corp, Somers, New York). The collected data followed the intent processing principle regarding baseline characteristics, which includes all participants assigned to the group. The primary objective of the trial is to evaluate the average 24-hour urge episodes, the average 24-hour urgency incontinence episodes and the score change in the ICI-Q-SF between the groups from baseline to weeks 4,8,24, and 32. The secondary outcomes include the 3-day urination diary(the average 24-hour urine volume and the average 24-hour micturition frequency), QUID and I-QOL. Independent sample *t* test is used for comparison between the 2 groups, and in case of non-normal distribution, non-parametric Wilcoxon statistics is used to test the null hypothesis. Paired *t* test is used for comparisons before and after treatment between the 2 groups. After comparison between the groups, independent sample *t* test is used if homogeneity of variance was met, while non-parametric Wilcoxon rank sum test is used otherwise. The *χ*^2^ test is used to assess the satisfaction and safety of the treatments. A *P* < .05 indicates that a difference is statistically significant.

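### Some eligibility criteria depend on events during the study, and intention-to-treat is tied to baseline characteristics, so randomised patients could be removed from the outcome analysis

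*Protocol article*

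**What the plan says.** Section 3.1 states that "only patients meeting all of the following criteria will be included". Inclusion criterion 4 is "No drug treatment during the study and no acupuncture treatment within 1 month prior to the study".

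Four exclusion criteria in section 3.2 also reach into the study:

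- criterion 2: "Patients with urinary tract infections or vaginal infections during the study period"
- criterion 3: "Patients undergoing implantable pelvic stimulator therapy during the study period"
- criterion 4: "Electrostimulation applied to patients in the pelvic region, back, and leg areas during the study period"
- criterion 5: "The use of drugs that can influence the outcomes before or during the study"

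Randomisation comes once eligibility is settled. Section 2.2 describes a 2-week baseline assessment and written consent, after which "eligible participants will be assigned with random numbers generated by a third party". Section 4.1 gives 8 weeks of treatment and 24 weeks of follow-up.

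On the analysis population, section 6 has one sentence: "The collected data followed the intent processing principle regarding baseline characteristics, which includes all participants assigned to the group". The article gives no rule for withdrawing a patient from the study or from the analysis.

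**The concern.** An eligibility criterion should be decidable before allocation. These five are not, because compliance over the following weeks is unknown when the envelope is opened. A patient who breaks one of them later has, on the literal text, turned out to be ineligible. That opens the way to leaving the patient out after allocation, possibly when the outcome is already known.

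The usual safeguard is a statement that all randomised patients are analysed as randomised for every outcome. Section 6 has the words for such a set but attaches them to baseline characteristics.

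The stake is the randomised comparison at weeks 4, 8, 24 and 32 on three primary outcomes. A patient who takes a bladder drug or seeks another stimulation therapy during follow-up is plausibly one who has not improved. If such patients leave the analysis, their arm looks better than it was, and the arms need not lose them equally.

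**Working it through.** **1. Can the criteria be applied at entry?**

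| Item | Refers to | Known at randomisation? | Link to response |
|---|---|---|---|
| Inclusion 4, exclusion 5 | drug use during the study | only the part before entry | plausible, the strongest of the four |
| Exclusion 3 | pelvic stimulator therapy | only if already in place | plausible |
| Exclusion 4 | other electrostimulation | only if already under way | plausible |
| Exclusion 2 | urinary or vaginal infection | only if already present | weak |

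The exposed period is 8 + 24 = 32 weeks. Exclusion criterion 5 names the time before the study and the time during it separately, so it cannot be read as covering entry status alone. Exclusion criterion 4 makes no exception for the trial's own stimulation in section 4.1; those two passages must be reconciled.

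**2. Does the article give a figure to reproduce?** No. It states no rate of exclusion after randomisation and no SD for any outcome. The 20% dropout allowance in section 5.5 is not an exclusion rate. What follows rests on assumptions.

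**3. Shift in one arm's mean.** Assume a normal response with higher values better, and remove exactly the worst fraction *p*. The mean of those who remain rises by φ(z_p)/(1 − p) SD, where φ is the standard normal density at the cut-off.

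- p = 10%: 0.1755/0.9 = 0.195 SD
- p = 20%: 0.280/0.8 = 0.350 SD

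In an arm of 50 these are the 5 or the 10 worst responders.

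**4. Direction.** From an assumed true difference of 0.50 SD in favour of electroacupuncture (EA):

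- removal from sham only: 0.50 − 0.195 = 0.305 SD, or 0.50 − 0.350 = 0.150 SD
- removal from EA only: 0.50 + 0.195 = 0.695 SD, or 0.50 + 0.350 = 0.850 SD

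**5. Both arms affected.** Simulation with 50 per arm, SD 1, a two-sample t test at 5% and 4,000 runs; the worst responders are removed at assumed rates. The type I error column comes from the same removal with no true difference.

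| Removed EA / sham | Estimate (true 0.50) | Power | Type I error |
|---|---|---|---|
| 0 / 0 | 0.50 | 70% | 4.5% |
| 10% / 10% | 0.50 | 76% | 8.9% |
| 4% / 10% | 0.40 | 57% | 10% |
| 10% / 20% | 0.35 | 49% | 18% |
| 4% / 20% | 0.25 | 29% | 30% |

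The 10% / 20% row agrees with step 3: 0.50 + 0.195 − 0.350 = 0.345. In the three unequal rows sham loses more poor responders, so with no true difference the mean estimate falls below zero (−0.10 to −0.26 SD) and the excess rejections favour sham.

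**The case against.** The strongest reply is that nothing in the article removes a randomised patient. Sections 3.1 and 3.2 work as an entry filter before randomisation, and the references to the study period may be loose wording for current or planned concurrent treatment. The sentence in section 6 is garbled: it opens with the collected data and ends with everyone assigned, so it may have been meant as intention-to-treat throughout. Detailed analysis sets and the handling of later events are commonly left to a full protocol or analysis plan.

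Much of this stands. A reader might infer that the protocol prescribes dropping these patients; it does not. The most that can be said is that the literal text permits it. What remains is a defect in wording that is on the page: criteria that cannot be assessed at entry, and an intention-to-treat statement whose stated scope omits outcomes. A later analysis plan that kept every randomised patient would sit awkwardly with eligibility text saying that such patients do not qualify.

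The reply is also right on size. Removing exactly the worst responders assumes a perfect link between response and exclusion, and doing so in one arm alone is the extreme case. The type I error figures for unequal removal assume that sham loses more patients even when the arms are truly equal, which non-response alone would not produce.

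**Conclusion.** The point holds as a wording defect that should be fixed, with moderate confidence. Five eligibility criteria depend on events after randomisation, and the stated intention-to-treat scope does not clearly cover the outcomes. Exclusion from the outcome analysis after allocation is therefore possible, though not ordered.

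The size of any bias is unknown. The shift of 0.20 to 0.35 SD in one arm is an upper-end illustration that rests on an assumed normal response, assumed removal rates and perfect selection of the worst responders. The most natural pattern, with more non-responders lost from sham, would shrink a true EA benefit; the opposite pattern would inflate it.

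Three stronger readings are not supported:

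- **Weeks 24 and 32 cannot be interpreted.** With no exclusion rate stated, the effect there could be negligible.
- **The shift can be set against the 19-point gap (59% − 40%) in section 5.5.** That needs an SD the article does not give. Section 5.5 also describes a difference in response rates, whereas the primary outcomes are changes in a score and in episode counts.
- **Every listed event is tied to response.** For infection the link is weak.

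**What to change.** 1. In sections 3.1 and 3.2, word each criterion as status at screening or at randomisation.
2. Move the prohibitions on concurrent treatment, unchanged in content, to a statement of how patients are managed during the trial. Reconcile exclusion criterion 4 with the trial's own stimulation.
3. State that drug use, other stimulation or infection after randomisation is recorded with date and arm, and that the patient stays in follow-up and in the analysis.
4. Amend section 6 so that intention-to-treat, meaning all randomised patients analysed as randomised, applies to all primary and secondary outcomes.
5. Report an analysis without these patients only as a per-protocol sensitivity analysis.

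The cost is a wording amendment to three sections, best made before outcome data are examined. The small downside is that outcomes after drug use or infection add some noise to the primary estimate.

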## Intervention

4

### The electroacupuncture group (EA)

4.1

Acupuncturists with more than 2 years of clinical experience, who have obtained the Chinese licensed physician certificate, are responsible for performing the acupuncture. The choice of intervention plan and acupoint is based on the expert's experience and based on previous studies.^[21,30–32]^ The acupoints of Ciliao (BLadder [BL]32), Zhongliao (BL33) and Huiyang (BL35) will be used (Table 1). All acupoints will be localized according to the name and location of acupoints drafted in 2006 by the National Standard of the People's Republic of China (GB/T 12346–2006). The electric stimulators (SDZ-V electroacupuncture apparatus), and stainless-steel sterilized needles (Huatuo disposable acupuncture needle; 0. 3 mm×50 mm/0. 3 mm×75 mm), were all purchased from the Suzhou Medical Appliance Factory of China. The electric stimulators will apply to the EA and to the sham electroacupuncture group (SA). During the treatment, participants will lie in the prone position, and the acupuncturists will use cotton balls soaked with 75% alcohol to sterilize the skin at the acupuncture site. After skin disinfection, sterile stainless-steel needles will be inserted into the selected acupuncture points. The needles are inserted approximately 50 to 60 mm into the skin with an angle of 60° in an inferomedial direction for BL32/BL33 and a slightly superolateral direction for BL35. After the insertion of the needle, for all needles perform small, equal manipulations of twirling, lifting, and thrusting to reach de qi (these sensations are composed of numbness, soreness, heaviness and swelling), it is considered to be an important component of acupuncture and moxibustion.^[33]^ Paired electrodes from the electroacupuncture apparatus were laterally connected to the needles’ handles of the bilateral BL32, BL33 and BL35. Acupuncture points are continuously stimulated with 100 Hz wave and a 1 to 5 mA electric current for 30 minutes. It is best to make the skin around the acupoint tremble slightly without pain. Participants were treated 3 times a week (every other day) for 8 weeks, with a total of 24 times, and 24 weeks of follow-up after treatment. The fixing pads are placed on the acupuncture points to keep the participants in a blind state.

**Table 1 T1:**
[figure not shown]
Locations of the acupoints.

### The SA group

4.2

The selected non-meridional and non-acupoint points are 20 mm from the level of BL32, BL33 and BL35, and the selected acupoint are away from the second lateral line of the Bladder Meridian (Fig. 2). During the treatment, participants will lie in the prone position, the skin is disinfected as in the EA group, and the fixation pad is attached to the acupuncture point. A 1.5-inch blunt needle (from Suzhou Medical Appliance Factory of China) is used to puncture through the fixed pad into the skin surface, then evenly twisted and turned, however, without piercing the skin. Paired electrodes from the electroacupuncture apparatus were laterally connected to the needles’ handles of the bilateral sham acupoints. The dedicated power supply cord is cut off, but the appearance is as usual; that is, the electroacupuncture indicator is on, but is actually not powered on. The frequency is 5 Hz and a current intensity of 0.1 to 0.5 mA. The treatment time, waveform and SDZ-V electroacupuncture apparatus are the same as those used for the EA group. The patients are told that it an effective slight current input will be applied that may not result in a sensation of stimulation. The treatment of the 2 groups of participants will be carried out separately in different rooms to avoid communication between the participants. At the end of the trial, participants were given 10 times free compensatory treatments.

**Figure 2 F2:**
[figure not shown]
Diagram of the acupoints and non-acupoints (the picture part comes from the internet).

## Outcomes

5

### Primary outcomes

5.1

a.The primary outcome measure is the score change in incontinence questionnaire-short form (ICI-Q-SF).Questionnaire ICI-Q-SF, scores ranging from 0 to 21, with higher scores indicating greater impairment, are compared with the baseline at the 4th (during treatment), 8th (after treatment), 24th (the first follow-up), and 32nd (the second follow-up) weeks of the study.ICI-Q-SF is the world's first universal incontinence assessment scale.^[34]^ which is mainly used to assess the frequency of incontinence, the causes of incontinence, and the impact of incontinence on the quality of life. Participants answered 4 questions related to symptoms based on their urination experience in the last week before the test. This includes the number of urine leaks, the amount of urine leakage, the impact of urine leakage on daily life, and when it occurs. The answers are recorded as 0 to 5 points, 0 to 6 points, 0 to 10 points, and the total score between 0 and 21 points. There is 1 unscored question, and the scale Cronbach's alpha coefficient was 0.92.^[34]^ The table is recommended as grade A by the Canadian urological association and the international urinary incontinence advisory committee, and as grade B by the European urological association. It is also recommended for the quantification of the severity of urinary incontinence by the UK's national institute of health and clinical excellence.b.The change in the average 24-hour urgency incontinence episodes, compared with the baseline and at the 4th, 8th, 24th and 32nd week.The 3-day urination diary is another valid, reliable and sensitive measure for patients with UUI. It has been translated into several languages, including Chinese, and is widely used in clinical records to indicate the number of urination during the day, nocturia, urgency, and urgency incontinence, as well as the amount of urine per urination and the amount of drinking water.^[35]^c.The change in the average 24-hour urge episodes, compared with the baseline and at the 4th, 8th, 24th, and 32nd week.

### Secondary outcomes

5.2

(1)The change in the average 24-hour urine volume, compared with the baseline and at the 8th and 32nd week.(2)The change in the average 24-hour micturition frequency compared with baseline and at the 8th and 32nd week.(3)The change in incontinence quality of life (I-QOL) scores, compared with the baseline and at the 8th and 32nd week.The I-QOL questionnaire is based on the satisfaction of participants on the improved quality of life associated with urination. The satisfaction of patients with the treatment was investigated through 3 aspects, namely behavioral limitations, psychological influence and social barriers. The higher the score, the better is the patient's quality of life.(4)Score of questionnaire for urinary incontinence diagnosis (QUID) at baseline.The English questionnaire QUID developed by Bradley^[36]^ et al was used as a tool to diagnose the type of urinary incontinence (SUI, UUI, MUI). The questionnaire includes 6 questions that are mainly focused on the conditions under which patients leak urine and the frequency of urine leakage. The first 3 questions are about SUI and the last 3 are about UUI. Each question has 6 options, each with a score of 0 to 5, and the final total score (0 - 30 points) is obtained by adding the scores of each question. Points on each of SUI and UUI can reach a maximum of 15 points. If the scores of the first 3 questions sum to ≥4, this could be considered as SUI diagnosis. Likewise, if the score of the last 3 questions is ≥6 can be considered UUI diagnosis. On the other hand, if the score of the first 3 questions is ≥4 and that of the last 3 questions is ≥6, the patient is diagnosed as MUI. Because the urgency incontinence and the stress urinary incontinence are easily confused, QUID is used as a mediator for diagnosing urinary incontinence. (Table 2)

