**Methods and analysis::**

A randomized, parallel, controlled study will be performed. Patients with UUI treated with electroacupuncture group (EA) will compare with the sham-treated sham EA (SA) patients. A total of 100 participants with UUI will be randomly allocated to either the EA or the SA group with a 1:1 ratio. The treatment of UUI patients will performed 3 times per week, for 8 weeks in 30-minute sessions. At the end of the treatment the patients will be followed-up until week 32. The primary outcomes include scores of incontinence questionnaire-short form, the average 24-hour urgency incontinence episodes, and the average 24-hour urge episodes responses from baseline until the 4th, 8th , 24th, and 32nd week. The secondary outcomes included the average 24-hour urine volume and the average 24-hour micturition frequency responses from baseline until the 8th and 32nd week, as well as the change in incontinence quality of life scores from baseline at the 8th and 32nd week. In addition, the degree of satisfaction of the participants undergoing acupuncture treatment will be measured at the 4th and 8th week. The participants’ clinical acupuncture expectations were evaluated at baseline, and the questionnaire for urinary incontinence diagnosis was used to identify stress incontinence, mixed urinary incontinence, and urge incontinence at baseline.

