## Discussion

7

The analysis of clinical trials of acupuncture treatment in UUI performed during the past 2 decades indicated that there are various methods for acupuncture treatment in UUI. Of these methods, electroacupuncture is the most frequently used, which can effectively improve symptoms such as urgency, frequent urination, and urinary incontinence. However, in clinical trials on UUI treatment with electroacupuncture, only few relevant studies included placebo control treatments,^[38,39]^ while most studies had insufficient clinical sample size^[39]^ and were performed using unclear research methods. Hence, the level of evidence obtained from these studies is not high. In this study, we are plan to compare the EA with a sham EA using standardized clinical research methods and objective quantitative evaluation indicators to verify the efficacy and safety of electroacupuncture on UUI patients. This study provides the scientific basis for a safety, more effective and easy-to-promote treatment of UUI patients in the future.

UUI patients often show urgency of urination, frequency of urination and urinary incontinence. The diagnosis is mainly based on the symptoms of the patients.^[11]^ Therefore, we use the ICI-Q-SF score, average 24-hour urge episodes and average 24-hour urgency incontinence episodes as the primary outcome to evaluate the clinical efficacy of electroacupuncture treatment of UUI. ICI-Q-SF is considered an effective, reliable and sensitive assessment method that is widely used in clinical practice.^[34]^ It is also a relatively simple questionnaire and the scores are easy to assess. Other widely used scales and questionnaires, such as the 3-day urination diary,^[35]^ I-QOL, QUID and the evaluation of clinical expectations of acupuncture, can also play subsidiary role in evaluating the results regarding the effect of acupuncture on improving the symptoms and ameliorating the quality of life of patients with UUI.

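### QUID is scored only at baseline but is listed and analysed as a secondary outcome, and the plan does not say what a mixed-incontinence QUID result means for eligibility or for ICI-Q-SF

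*Protocol article*

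**What the plan says.** Section 5.2 (Secondary outcomes) has four items. The first three are changes from baseline to weeks 8 and 32. The fourth is "Score of questionnaire for urinary incontinence diagnosis (QUID) at baseline". The same section explains that QUID classifies the type of incontinence. Three stress items sum to at most 15 and count as stress type from 4 upwards. Three urge items sum to at most 15 and count as urge type from 6 upwards. Reaching both thresholds means mixed incontinence. It adds that stress and urge incontinence are easily confused and that QUID serves as a diagnostic aid.

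The abstract agrees on timing and purpose: "the questionnaire for urinary incontinence diagnosis was used to identify stress incontinence, mixed urinary incontinence, and urge incontinence at baseline".

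Section 6 (Statistical methods and analysis) nevertheless states: "The secondary outcomes include the 3-day urination diary(the average 24-hour urine volume and the average 24-hour micturition frequency), QUID and I-QOL". The next sentence begins "Independent sample *t* test is used for comparison between the 2 groups", with a Wilcoxon test as the fallback. Section 7 (Discussion) says that "I-QOL, QUID and the evaluation of clinical expectations of acupuncture, can also play subsidiary role in evaluating the results".

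Section 3.1 (Inclusion criteria) requires a urologist's diagnosis of urge urinary incontinence (criterion 1) and "Frequent urination, urgency, and urinary incontinence" with difficulty in controlling urination (criterion 3). Neither section 3.1 nor section 3.2 (Exclusion criteria) mentions QUID, stress incontinence or mixed incontinence.

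**The concern.** An outcome must be measured at a time when treatment could have changed it. QUID is not, so it has no place among the outcomes. Following sections 5.2 and 6 literally would put a comparison of baseline QUID scores in the secondary efficacy results, where a chance imbalance could be read as a finding.

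The real use of QUID is to describe who was enrolled, and the plan does not follow that use through. It collects a measure of stress and mixed incontinence, with cut-offs, and does not say what happens when the result is mixed. Two screeners could treat such a patient differently and both comply. This matters most for ICI-Q-SF, which scores leakage of any kind. Stress leakage in mixed patients adds variation to that score that has nothing to do with urgency, and it may dilute the treatment effect.

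**Working it through.** **1. When QUID is measured and how it is used**

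| Place | Timing | Role given to QUID |
|---|---|---|
| Abstract, Methods and analysis | Baseline | Identifies incontinence type |
| Section 5.2, item 4 | Baseline | Secondary outcome, and diagnostic aid |
| Section 6 | None given | Secondary outcome, directly before the between-group tests |
| Section 7 | None given | Subsidiary role in evaluating results |

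Both places that give a time say baseline. Table 2 (measurement time points) is not reproduced in the text at hand, but nothing in the text suggests a second QUID measurement.

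**2. What a between-group test of baseline QUID can show**

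Under proper randomisation both groups' baseline scores come from the same distribution. The null hypothesis is therefore true by design, whatever electroacupuncture does. With the P < .05 rule in section 6, the chance of a significant result is about 0.05, or 1 in 20, and that result carries no information on efficacy.

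**3. Who can be enrolled**

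- QUID ranges: 6 items × 5 points = 30 in total, and 3 × 5 = 15 per subscale. Both match section 5.2.
- Pure stress incontinence fails criterion 1 (urge diagnosis) and criterion 3 (urgency). It can enter only by misdiagnosis.
- Mixed incontinence: a patient diagnosed with urge incontinence by the urologist, with frequency, urgency and leakage, who scores at least 4 on the stress items and at least 6 on the urge items, breaches no entry criterion through that QUID result.

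**4. Which primary outcomes the stress component reaches**

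- ICI-Q-SF (section 5.1): the scored ranges are 0 to 5, 0 to 6 and 0 to 10, and 5 + 6 + 10 = 21, the stated maximum. Four questions are listed and one is unscored. Going by the order of the list, the unscored one is when leakage occurs. The score therefore counts the number of leaks, their amount and their impact whatever the cause, and stress leakage enters in full.
- The two diary outcomes count urgency incontinence episodes and urge episodes. Stress leakage is not part of either definition.

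**5. Illustration for ICI-Q-SF only, resting on assumptions**

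The documents give neither the share of mixed patients nor their response. Take the stated 80% power at face value, with 50 × 0.8 = 40 evaluable per group (section 5.5). A two-sided 5% t test with 40 per group has 80% power at a standardised difference d = 0.634. This d is solved back from the sample size and is not stated in the plan. If a share m of patients loses a fraction k of the effect, the average effect is multiplied by 1 − k × m, and the noncentrality is 0.634 × (1 − k × m) × √20.

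| Assumed effect in mixed patients | 10% mixed | 30% mixed | 50% mixed |
|---|---|---|---|
| Three quarters (k = 0.25) | 78% | 74% | 69% |
| Half (k = 0.5) | 76% | 66% | 56% |
| None (k = 1) | 71% | 50% | 29% |

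For the half-effect row, the multipliers are 0.95, 0.85 and 0.75, and the noncentralities are about 2.69, 2.41 and 2.13. The spread, from 78% to 29%, shows how far the answer depends on the assumptions.

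**The case against.** Several points on the other side have weight.

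- **Stress incontinence.** A reader might infer that patients with pure stress incontinence can be randomised. The criteria do not allow it: criteria 1 and 3 both stand in the way. This objection stands in full.
- **QUID and entry.** A reader might infer that QUID plays no part in selecting patients. Section 5.2 calls it an aid to diagnosis, so it may inform the urologist's decision under criterion 1. This stands. What is left is narrower: the consequence of a mixed or stress result is not stated.
- **The test is implied, not specified.** Section 6 names no test for QUID specifically, the abstract sets QUID apart from the secondary outcomes, and the score is openly labelled as baseline. This limits the harm, since many readers would recognise a baseline comparison. It does not remove the error, because sections 5.2, 6 and 7 all give QUID an outcome role.
- **Covariates belong in an analysis plan that is not shown.** Fair: the lack of a covariate is not in itself a fault. Adjustment is offered as an improvement that uses data already collected. It would, however, replace the unadjusted test that section 6 now names.
- **Power.** A reader might infer a definite loss of power. The shares, the reduced effect and d are all assumed, and section 5.5 plans on reductions of 40% and 59%, not on a standardised mean difference. Two of the three primary outcomes count urge events only. The figures do not support a claim about the trial as a whole.
- **Excluding mixed patients.** The document does not say that it targets urge incontinence without any stress component. A QUID exclusion would change the population and slow recruitment, so it is a trade-off and not a correction.

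**Conclusion.** The classification error is certain and rests on no assumption: a score taken only before treatment is presented as a secondary outcome in sections 5.2 and 6 and given an efficacy role in section 7. Its direct effect is small: one uninformative test with about a 5% chance of a spurious result.

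The eligibility gap is real for mixed incontinence. The documents do not support extending it to pure stress incontinence. Its statistical consequence falls mainly on ICI-Q-SF and cannot be sized from the documents. The power table is an illustration under assumed shares and assumed response, and should not be quoted as an expected loss.

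**What to change.** 1. Remove QUID from the secondary outcomes in sections 5.2 and 6, and from the sentence in section 7 that gives it a role in evaluating results. List it as a screening and baseline measure, reported descriptively by group. Cost: wording only.
2. Compare ICI-Q-SF change between groups with a regression (ANCOVA) that includes the baseline QUID stress score (first three items), in place of the unadjusted t test, and fix this before the data are unblinded. The questionnaire is already collected. Adjustment removes variation explained by the stress score. It does not restore an effect that is truly smaller in mixed patients. Cost: a little more analysis work.
3. State in section 3 whether a QUID result of mixed or stress type affects eligibility, and if it does not, say so. No new exclusion is proposed here. This costs a sentence, and screen failures would rise only if the sponsor chose to make QUID an entry rule.
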